#### Allocation concealment mechanism

Ass allocation concealment mechanism, the authorized study personnel, who perform randomization, are not involved in the inclusion of patients as well as in the treatment part.

#### Blinding

To reduce bias blinding of study contributors is a common and effective measure [10]. However, in our study, only patients were blinded to the study treatment. Surgeons cannot be blinded as they perform the study therapy. The data analyst, data collector, and the outcome assessor were not blinded due to the robust outcome parameters.

### Study visits and data collection

This trial consists of a total of seven study visits, which take place at the following times and include the following milestones of the trial (Table 2):Preoperative at the first consultation or at the day before surgery: verification of all eligibility criteria (inclusion and exclusion criteria), obtaining patient informed consent, completing the screening form including laboratory resultsDay of operation: randomization, performing hepaticojejunostomy in the randomized surgical technique, completing the surgical formPostoperative day 1 (POD 1): completing the morbidity and mortality form including laboratory results and an intraabdominal drainage analysis of bilirubinPostoperative day 3 (POD 3): completing the morbidity and mortality form including laboratory results and an intraabdominal drainage analysis of bilirubinDay of discharge: completing the discharge form including the morbidity and mortality formThree and 12 months after operation: completing the morbidity and mortality form by telephone interview

**Table 2 Tab2:** Visit schedule of the HEKTIK trial

	Study period						
	Screening at first consultation or at the day before surgery	Day of operation	POD 1	POD 3	Day of discharge	3 months after operation	12 months after operation
In-/exclusion criteria	X						
Patient informed consent	X						
Screening form	X						
Laboratory tests	X		X	X			
Randomization		X					
Used surgical technique		X					
Surgical form		X					
Morbidity and mortality form			X	X	X	X	X
Drainage analysis			X	X			
Discharge form					X		
Telephone interview						X	X

Preoperative and postoperative stationary data are collected by the investigators, operative data by the operating surgeon and the data at three months postoperative by authorized study personnel.

The screening form contains demographic data including basis data, disease course, and comorbidities as well as preoperative blood results (including hemoglobin, white blood cells, creatinine, albumin, serum c-reactive protein, and liver enzymes). In the surgical form data about the operation like duration and kind of surgery as well as data about the hepaticojejunostomy (duration, suture material, information about the hepatic duct) is recorded. The postoperative forms include always the documentation of morbidity and mortality as well as at POD 1 and 3 laboratory results (including hemoglobin, white blood cells, creatinine, albumin, serum c-reactive protein, Quick, bilirubin as well as liver enzymes and cholestasis parameters) and the bilirubin concentration in the abdominal drain being close to the hepaticojejunostomy. At discharge histological results and length of hospital stay are additionally documented.

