## Abstract

**Background:**

Hepaticojejunostomy is commonly performed in hepato-bilio-pancreatic surgery, particularly during pancreaticoduodenectomy. The purpose of this study is to evaluate the safety and efficiency of two commonly applied suture techniques (the interrupted versus the continuous suture technique) in patients undergoing a hepaticojejunostomy during pancreatoduodenectomy.

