**Methods:**

The HEKTIK trial is a multicenter, randomized controlled, patient-blinded surgical explorative trial with two parallel study groups. An adaptive sample size design was chosen: First, 100 patients scheduled for surgery including a hepaticojejunostomy will be randomized 1:1 either to the interrupted suture technique or the continuous suture technique after informed consent. Based on this data, needed sample size will be adjusted.

The primary endpoint will be the occurrence of anastomotic leakage of hepaticojejunostomy, defined as bilirubin concentration in the drain fluid at least 3 times the serum bilirubin concentration on or after postoperative day 3 or as the need for radiologic or operative intervention resulting from biliary collections or bile peritonitis (according to the definition of ISGLS). Further perioperative parameters like other morbidities as well as duration and costs of the hepaticojejunostomy will be analyzed as secondary outcomes.

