## Background

Hepaticojejunostomies represent a common step during pancreatic and liver surgery including partial pancreatoduodenectomy, major liver resections, and bile duct resections. Overall, a hepaticojejunostomy is considered as a safe procedure with low rates of postoperative complications including a leakage rate of 2.3% to 5.6% [1, 2]. However, failure of this anastomosis leads to considerable consequences with a high risk of prolonged hospitalization and the need for interventional drainage or re-laparotomy, which is associated with high morbidity and mortality, even in high volume centers [3, 4]. Known risk factors for leakage are previous chemoradiation, preoperative biliary drainage, impaired liver synthesis capacity, malnutrition, obesity, and anastomosis at the level of hepatic duct bifurcation [1].

However, leakage of a hepaticojejunostomy could always be associated with the surgical technique used. There are especially two common techniques used for hepaticojejunostomy: the interrupted suture technique and the continuous suture technique. According to a current national survey in Germany 56% of the participating hospitals stated that they use both techniques for performing a hepaticojejunostomy depending on the surgical sites, while 40% of the hospitals adhere always to one of the mentioned two techniques. These results show a relevant heterogeneity of the techniques used among hospitals in Germany [5]. There is an ongoing debate between advocates of both techniques, who argue with universal use (also for small ducts) and a potentially lower stenosis rate for the interrupted suture technique and with a better sealing of the anastomosis and operative time saving for the continuous suture technique.

Despite the frequent necessity of hepaticojejunostomies in surgery and the relevant consequences for the patient with leakage, there are no randomized studies to compare the different surgical techniques. For this reason, the presented randomized controlled multicenter trial was initiated to assess whether there is a significant difference in the occurrence of anastomotic leakage between the two groups interrupted suture versus continuous suture technique for performance of a hepaticojejunostomy during pancreatoduodenectomy.

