### Surgical technique

The hepaticojejunostomy will be performed as a part of pancreatoduodenectomy and can be placed on the same jejunal loop as the pancreatojejunostomy or on a second jejunal loop.

The common preparation before suturing the hepaticojunostomy includes an opening of the hepatic duct with corner sutures and an antimesenterical jejunal incision. After the corner sutures are placed at the hepatic duct, the diameter of the ductus hepaticus is measured in mm and documented in the CRF.

The further procedure depends on the randomized technique:Interrupted suture technique: with this technique both the posterior and the anterior walls are performed single-rowed using interrupted stitches.Continuous suture technique: with this technique both the posterior and the anterior walls are performed single-rowed using continuous sutures.

There are no specifications for the suture material and the number of sutures used, but these data will be documented in the CRF. If an anastomotic leakage is detected intraoperatively, any number of interrupted sutures may be added to the hepaticojejunostomy. The measurement of the duration of the hepaticojeunostomy begins with the first suture (excluding the corner sutures of the hepatic duct) and ends with the cutting of the last thread, which is necessary to complete the hepaticojeunostomy. The application of an abdominal drainage near the hepaticojejunostomy is standard in our department and is recommended, but not mandatory.

Used suture material, number of sutures, number of interrupted stiches, number and place of abdominal drains, and the time for hepaticojejunostomy are documented in the CRF. In addition, the surgeon’s experience performing hepaticojejunostomies is recorded and documented in the CRF.

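### The hepaticojejunostomy duration, a secondary endpoint, is supplied by the unblinded operating surgeon, and its stop event is silent on sutures added for an intraoperative leak

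*Protocol article*

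**What the plan says.** Four statements in the protocol article bear on this point.

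- **Who collects.** Study visits and data collection divides data collection by role and gives "operative data by the operating surgeon". The same section describes the surgical form, on which "data about the hepaticojejunostomy (duration, suture material, information about the hepatic duct) is recorded".
- **Who is blinded.** Under Blinding, only patients are. "Surgeons cannot be blinded as they perform the study therapy". For everyone else the reason given is: "The data analyst, data collector, and the outcome assessor were not blinded due to the robust outcome parameters".
- **What is timed.** Surgical technique starts the clock at the first suture, not counting the corner sutures on the duct. The interval "ends with the cutting of the last thread, which is necessary to complete the hepaticojeunostomy". The same section allows any number of interrupted sutures to be added when a leak is found during the operation.
- **What the outcome is for.** The abstract gives the purpose as to "evaluate the safety and efficiency of two commonly applied suture techniques", and says that "duration and costs of the hepaticojejunostomy will be analyzed as secondary outcomes". Aim of the study and study endpoints lists the duration among the secondary endpoints, alongside total operative time and material costs.

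**The concern.** The person who provides the measurement is the person being measured, and that person knows the allocation. Blinding the surgeon is impossible, as the protocol says, but that does not oblige the surgeon to be the source of the time. The robustness argument under Blinding fits a laboratory bilirubin value well. It does not clearly cover a number of minutes supplied by the operator.

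There is also a documented expectation about the result. The Background reports that advocates argue "with a better sealing of the anastomosis and operative time saving for the continuous suture technique". An outcome on which the field already holds a view is one where the source of the measurement should be kept apart from the operator if that is easy to do.

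At stake is how far a difference in duration between the arms can be believed. If part of it came from reporting, recruiting more patients would not remove that part.

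**Working it through.** The protocol gives no standard deviation, expected difference or power for duration, so it has no figure of its own to reproduce. The check is mainly a reading of the sections together.

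**Step 1: is the assignment stated or inferred?** Duration is on the surgical form, operative data are collected by the operating surgeon, and the surgeon is unblinded. All three are stated. The article does not say who reads the clock, or whether the time is measured or recalled.

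**Step 2: how tight is the definition?** The start is a single observable event. The stop is the cutting of the last thread needed to complete the anastomosis. Two readings are open when a leak is seen during surgery and interrupted sutures are added:

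- the anastomosis was complete before the repair, and the added sutures lie outside the interval;
- it was complete only after the repair, and they lie inside it.

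The text does not choose between them. The choice would fall to whoever records the time, and it would matter most if repair were needed more often in one arm.

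**Step 3: would the stated checks find a discrepancy?** Data monitoring and quality assurance has all case report forms inspected together with documents such as the surgery report and discharge letter, without monitoring visits. The article does not say that either document holds a separately recorded anastomosis time.

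**Step 4: what does the endpoint affect?** Under Statistical considerations and sample size calculation, the decision to continue and the new sample size depend on the primary endpoint, leakage. Duration enters neither.

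**Step 5: illustration only.** Suppose there is no true difference but a reporting shift between arms of b standard deviations. The shift is assumed, not taken from the documents. With n per group, SE = √(2/n) in SD units, and the two-sided 5% rejection probability (normal approximation; sidedness is assumed) is

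P(Z > 1.96 − b/SE) + P(Z < −1.96 − b/SE).

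| n per group | SE (SD units) | b = 0.1 | b = 0.2 | b = 0.3 |
|---|---|---|---|---|
| 50 (first stage) | √(2/50) = 0.200 | 7.9% | 17.0% | 32.3% |
| 1000 (protocol's cap) | √(2/1000) = 0.045 | 60.9% | 99.4% | 100.0% |

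For example, at n = 50 and b = 0.2, b/SE = 1, and P(Z > 0.96) + P(Z < −2.96) = 0.1685 + 0.0015 = 0.170. The table shows only that a larger sample does not dilute a systematic shift. It says nothing about whether a shift exists here.

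**The case against.** The case against is substantial, and much of it stands.

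- **Collecting is not estimating.** A reader might infer that the surgeon guesses the time afterwards. The documents do not support that. A surgeon who is suturing may well take the times from a theatre clock or from staff and only enter them. This stands, and the point is limited to who supplies the value.
- **The article is condensed.** The case report form and the full protocol are not shown, and start and stop fields may exist there. This is fair as to form fields. The allocation of the task to the surgeon, however, is stated in the article.
- **The events are defined.** The start and stop rules are a real safeguard and limit the latitude. This stands, except for the added sutures.
- **Preference among trial surgeons is not shown.** It is tempting to cite the national survey, in which 40% of hospitals always keep to one technique. That figure describes hospitals in a survey, not the trial's operators, and 56% reported using both. Randomization also takes place only when the surgeon judges both techniques suitable. Since the Background describes advocates on both sides, even the direction of a shift is unknown.
- **The remedy is partial.** A theatre colleague sees the technique too, may rely on the surgeon to say when the anastomosis is finished, and cannot prevent an operator from working faster in a favoured arm. This stands.
- **Importance.** Calling this the trial's direct efficiency outcome goes too far, because total operative time and material costs also bear on efficiency and no endpoint carries that label.

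**Conclusion.** The point holds as a modest weakness in how one secondary endpoint is measured. The documents place collection of the duration with the unblinded operator, the reason given for unblinded assessment does not clearly extend to it, and the stop event leaves leak-repair sutures undecided.

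The size and direction of any bias cannot be derived from the documents. The percentages in the table rest wholly on assumed shifts and should not be quoted as an estimate for this trial. A reader might go further and infer that a time difference found here would be an artefact, or that the main result is compromised. Neither follows: nothing shows that the times are misreported, and the leakage comparison and the sample-size decision do not use duration. This is an inexpensive improvement, not a flaw that threatens the trial.

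**What to change.** In Surgical technique and in Study visits and data collection:

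1. Have a member of the theatre team who is already present but not operating log two clock times: the first stitch after the corner sutures, and the cutting of the final thread.
2. State whether interrupted sutures added for a leak found during surgery count towards the interval, with the same rule in both arms. Without this, the second clock time inherits the same ambiguity.
3. Derive the duration endpoint from these two times only. The surgeon can go on documenting duct diameter, suture material and stitch numbers.
4. Recruitment was under way when the article appeared, so flag patients whose times were supplied by the surgeon and repeat the comparison without them.

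The cost is two extra fields, a sentence or two of protocol text and a short instruction to theatre staff. No extra personnel are needed. The recorder would remain unblinded and true differences in operating speed would remain, so the gain is confined to operator reporting bias.

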### Post-trial care

In addition to the two calls after 3 and 12 months postoperatively to record morbidity, there is no specific follow-up program for the included patients. Further follow-up care depends in particular on the underlying disease: e.g. if pancreatic carcinoma is present, we would offer a quarterly follow-up check-up in the first year and after that a follow-up every 6 months.

### Documentation and data management

The collected data is documented using a case report form (CRF) with pseudonymization of patients. For data protection, the CRF contains only an individual identification code including a center number and a patient number. All CRFs are reviewed by the investigators. All data collected is treated with strict confidentiality in accordance with the data protection and the GCP guidelines. Access to the data is only permitted to authorized personnel.

### Data monitoring and quality assurance

Data monitoring and quality assurance are guaranteed by an inspection of all CRFs together with other documents such as the surgery report and the discharge letter. Therefore there is no data monitoring committee (DMC) as well as no data monitoring visits, as the risk of study bias through missing extended monitoring is considered low. There is no mandatory intraoperative photo documentation of the hepaticojejunostomy. Since there are only limited technical requirements for the performance of the hepaticojejunostomy, the risk of deviations from the study protocol should be low. In addition, the anatomical and surgical characteristics (such as the number and type of suture material, nature of the hepatic duct) are recorded in the CRF.

The trial can be stopped by the coordinators of the trial in case of reasons recommending termination of the trial like medical or ethical rationales as well as inadequate patient recruitment or additional external evidence.

### Assessment of safety

Any deviations from the normal postoperative course will be documented in a special morbidity form during the whole study period (from signature of the informed consent until 12 months postoperative) and classified according to the Clavien-Dindo classification. The morbidity form record the symptoms, the diagnostics and therapy taken and the beginning, severity, duration, consequences, and outcome of the event as well as to what extent a causality with the trial intervention is possible.

A major morbidity event (Clavien-Dindo ≥ 3) must be reported to the sponsor by the responsible investigator within 24 hours after their occurrence. The heads of this trial are responsible for the assessment of these events and the possible need to notify the responsible ethics committee.

### Ethical aspects

The trial is to be conducted in line with the Declaration of Helsinki. All trial documents (study protocol, CRF, patient information, informed consent) were approved by the ethical committee of the Friedrich-Alexander-university Erlangen-Nuremberg (number: 167_19 B; decision on 22.05.2019). All screened patients will be informed in detail about the study and possible risks. All further participating centers have to obtain approval from their local ethics committee.

### Statistical considerations and sample size calculation

Literature was systematically reviewed to identify all published data to this topic (see Supplementary Fig. 1). There were no randomized controlled trials and only one retrospective analysis from Japan, which compared the interrupted suture technique with the continuous suture technique in the setting of liver transplantations [11]. However, these data are not suitable for a meaningful sample size calculation, as the leakage rates of this reported trial come from a different setting and seem to be high compared to data derived mainly from hepaticojejunostomies only or as part of a pancreatoduodenectomy (5.6% using interrupted sutures [1] and 2.3% using both techniques [2], respectively).

Therefore, an adaptive sequential sample size design was chosen: The sample size per patient group was set exploratively at a group size of 50 patients. Total sample size was 100 patients. The prevalence of the primary endpoint in the 100 patients examined then forms the data basis for an adequate further sample size analysis and consequently for a sample size adjustment. To proceed the study with the then new calculated sample size, some criteria have to be met: First, the absolute difference in the primary endpoint must be at least 1% to justify clinical relevance of the study. Second, the calculated sample size per group should not exceed 1000 patients in order to be able to meaningfully end the study.

Due to the design with multiple testing an error correction will be performed in statistical analysis. Due to the lack of reliable data in the literature, this adaptive design offers the best opportunity to get meaningful data with adequate power.

Statistical analysis will be performed using SPSS software. An intention-to-treat and a per-protocol-analysis will be used for the analysis of the primary outcome. Comparisons of metric and ordinal data will be calculated with the Student *t*-test or Mann-Whitney *U* test. The chi-square test was used for categorical data. Statistical significance will be set at *p* < 0.05.

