## Discussion

This clinical trial is one of the first randomized controlled study to investigate the safety and efficiency of two commonly applied suture techniques (the interrupted versus the continuous suture technique) in patients undergoing a hepaticojejunostomy during pancreatoduodenectomy. In addition to this study, there could be identified a second ongoing registered study on the same issue in China (ChiCTR1900020605).

Although the performance of a hepaticojejunostomy is a common procedure in hepato-pancreato-biliary surgery and a leakage of this anastomosis is associated with relevant morbidity and mortality, very few studies have dealt with this topic to date. A comparison of the suturing techniques with regard to the leakage rates was only carried out in one retrospective study in the setting of liver transplantations. This illustrates the necessity and usefulness of a study to compare the suturing techniques for hepaticojejunostomy during pancreatoduodenectomy.

Before initiating the present trial, a Germany-wide survey was carried out on the application of the various suturing techniques for hepaticojejunostomies. This confirmed that there is enormous heterogeneity in the technology used. While the majority use both techniques depending on the intraoperative situs, 40% of those questioned are rigidly attached to their technique. The bile duct diameter was cited as the most important decision criterion for those who use both techniques. This shows that very small bile ducts in particular can often be better treated using the interrupted suture technique. Therefore, the lower limit of the bile duct diameter in our study was set to 5 mm.

Due to the small amount of data comparing surgical techniques for hepaticojejunostomies, the sample size calculation is a particular challenge. There are only data available comparing the interrupted and the continuous suture technique in the liver transplant setting, where the risk of leakage is likely to be higher. Published data from the pancreatic surgery setting show lower leakage rates. However, in this pancreatic setting, there are no comparative data. To compensate for this lack of data, an adaptive design with an interim analysis after 100 patients was incorporated. At this point in time, the sample size can be adjusted, which significantly increases the accuracy of the sample size calculation.

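### Continuation, and on the natural reading the final size, rest on a difference observed in 50 patients per group, so the claim of adequate power is not supported

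*Protocol article*

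**What the plan says.** All the rules are in the protocol article, section Statistical considerations and sample size calculation. The first stage has no derivation: "The sample size per patient group was set exploratively at a group size of 50 patients", and "Total sample size was 100 patients". The interim step is "The prevalence of the primary endpoint in the 100 patients examined then forms the data basis for an adequate further sample size analysis". Two conditions govern continuation. One is "First, the absolute difference in the primary endpoint must be at least 1% to justify clinical relevance of the study"; the other is that the recalculated size should be no more than 1000 per group.

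The leak rates cited from settings closer to this trial are "5.6% using interrupted sutures [1] and 2.3% using both techniques [2], respectively"; the Background gives the same range. The section states no planning difference, no numerical power and no leak rate for continuous suturing alone.

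Two claims are made for the design. The statistical section says that "this adaptive design offers the best opportunity to get meaningful data with adequate power". The Discussion says that after 100 patients "the sample size can be adjusted, which significantly increases the accuracy of the sample size calculation".

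**The concern.** Anastomotic leakage is rare, so 100 patients yield only a handful of events. A difference between two groups of 50 is then mostly noise, yet the plan uses it as a go/no-go criterion and appears to use it as the effect for the new sample size.

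That creates two errors that do not cancel. If chance makes the difference large, the second stage is too small for the true effect. If chance makes it small or zero, the trial stops. At stake is whether the primary question can be answered: a real difference of the size suggested by the cited rates would usually be missed, although the sample it needs lies inside the plan's own limit of 1000 per group.

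**Working it through.** **Inputs from the article.** 50 per group, 1:1 allocation, cited rates of 2.3% and 5.6%, continuation if the observed difference is at least 1% and the new size is at most 1000 per group, chi-square test, significance level 0.05.

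**Assumptions.**
- Two-sided testing; target power 80%, with 90% as a check.
- True rates of 5.6% versus 2.3%. The 2.3% comes from a source that mixed both techniques.
- The new size is computed from the observed rates in each group.
- One final chi-square test on the data of both stages.

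There is no stated calculation to reproduce, because the 50 per group is declared exploratory.

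**1. Information at the interim.** Expected leaks in 100 patients are 50 × 0.056 + 50 × 0.023 = 3.95, or 2.3 to 5.6 if both groups share one of the cited rates. The standard error of the difference is √[(0.056 × 0.944 + 0.023 × 0.977)/50] = 0.0388. The 95% half-width is 1.96 × 3.88 = 7.6 points, against an assumed true difference of 3.3 points.

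**2. The 1% criterion.** With 50 per group one leak is 2 points, so the smallest non-zero difference is 2 points. The criterion excludes exact ties and nothing else.

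**3. Size needed.** n per group = [1.96 √(2p̄(1−p̄)) + 0.842 √(p₁(1−p₁) + p₂(1−p₂))]² / (p₁−p₂)². For 5.6% versus 2.3%, p̄ = 0.0395 and n = (0.5399 + 0.2310)² / 0.033² = 0.5943 / 0.001089, which rounds up to 546 (731 at 90% power).

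**4. The same formula on possible interim counts (80% target).**

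| Leaks, group by group | New size per group | Result |
|---|---|---|
| 1 vs 0 | 388 | continue |
| 2 vs 0 | 192 | continue |
| 2 vs 1 | 1141 | stop |
| 3 vs 1 | 376 | continue |
| 3 vs 2 | 1863 | stop |

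**5. Operating characteristics.** Every pair of interim counts was weighted by its binomial probability and followed to the final test.

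| True rates | Tie, stop | Above 1000, stop | Continue | Significant at end |
|---|---|---|---|---|
| 5.6% vs 2.3% | 15.2% | 21.3% | 63.5% | 36.5% |
| 8% vs 4% | 12.2% | 22.5% | 65.3% | 39.4% |
| 2.3% in both | 28.5% | 19.4% | 52.2% | 4.2% |
| 4.0% in both | 21.0% | 29.2% | 49.9% | 4.6% |
| 5.6% in both | 17.7% | 30.3% | 52.0% | 5.1% |

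At 5.6% versus 2.3% the stops add up to 15.2% + 21.3% = 36.5%; that this equals the power is coincidence. Among continuing trials the new size has median 192 per group (10th to 90th percentile 93 to 388), and about 8% reach 546. With a 90% target overall power is 41.9%. If the announced error correction lowered the final level to 0.025, with the size still computed at 0.05, power would be 28.5% (80% target) or 34.4% (90% target).

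**6. The two conditions together.** A true difference of 1 point needs 4272 per group (3.3% vs 2.3%) to 7597 (5.6% vs 4.6%). At these rates the difference named as clinically relevant cannot be adequately sized within 1000 per group.

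**7. If only the pooled rate is used for sizing.** The 1% criterion still acts on the observed difference. It is passed in 100 − 15.2 = 84.8% of trials at 5.6% versus 2.3%, and in 71.5% to 82.3% with equal rates. It hardly separates the two situations.

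**The case against.** The strongest objection is that the article says prevalence, not prevalence by group. If the pooled rate were combined with a difference set in the full protocol or analysis plan, the median of 192 and the 36.5% power would not apply. That is fair, and the by-group reading is an assumption. It is the natural one, because the only difference in the section is the observed one in the continuation rule. On the pooled reading the objection to the 1% criterion remains (step 7).

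Second, no power figure and no continuous-only rate are given, so 80% and 5.6% versus 2.3% are the reviewer's choices. This also stands, but the result does not hang on them: at a 90% target, or at 8% versus 4%, power stays near 40%.

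Third, the abstract calls the trial explorative. Yet the Background and the trial design section aim to detect a significant difference, and the statistical section claims adequate power.

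A reader might also infer more than the documents support:
- That the interim interval is wider than any plausible effect. The documents do not bound the plausible effect.
- That the accuracy statement is simply false. The Discussion compares the interim data with having no comparative data at all. The supported statement is that the gain is not shown, and that the rule as read gives sizes far from the one needed.
- That a stop at 100 will be reported as equivalence. No section plans such a claim; the risk is only that a stop under a criterion labelled clinical relevance could be misread.
- That type I error is inflated. In the scenarios run it stayed at about 4% to 5%.

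**Conclusion.** The point holds. This is not a detail left to another document: the stated 1% and 1000-per-group rules, followed as written, make continuation only modestly more likely with a real difference (63.5%) than with none (50% to 52%). On the by-group reading the second stage is usually far too small, and overall power is about 36%, or 42% with a 90% target. These figures rest on the assumed true rates, two-sided 0.05 and the assumed power target. If sizing uses only the pooled rate, the finding narrows to the 1% criterion, which excludes only ties. On either reading the article gives no support for its claim of adequate power or for a significant gain in accuracy.

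**What to change.** Choose one of two changes.

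**(a) Blinded re-estimation.** Drop the criterion on the observed difference. State a relevant difference now, before anyone looks at leaks by group; this matters because the Blinding section leaves the analyst and outcome assessor unblinded. At 100 patients, compute the size from that difference and the pooled leak rate only. With 3.3 points and 80% power, 2, 3, 4, 5, 6 and 7 pooled leaks give 282, 419, 553, 684, 812 and 938 per group; 8 give 1060. Two rules must be written down:
- The size for 0 or 1 pooled leaks, where one group's rate would be negative and the formula is undefined. This happens in 9.0% of trials at 5.6% versus 2.3%.
- Whether a result above 1000 per group is capped or stops the trial. The present text makes 1000 a condition for proceeding, so a cap would be a change.

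Power at 5.6% versus 2.3% under these choices:

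| Size for 0–1 leaks | Capped at 1000 | Stop above 1000 |
|---|---|---|
| stop at 50 per group | 71% | 68% |
| 282 per group | 75% | 72% |
| 1000 per group | 80% | 77% |

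Type I error is about 5% or lower. The cost is an amendment and a larger likely second stage: median 553 per group, or 1106 patients. That is within the limit the plan already accepts, but it is a real burden, since only one centre was recruiting at the time of writing.

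**(b) Restatement.** Delete the adequate-power and accuracy claims. Present the 100 patients as a pilot that reports the leak rates and their difference with confidence intervals, and state that a stop at 100 is not evidence of no difference. This costs only wording.
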